**Fig. 2 Fig2:**
[figure not shown]
Mini-AFTERc pilot trial timeline, following SPIRIT [26]

Patient involvement is a core principle in the design and implementation of this pilot trial. [name] (EB) is a representative of the National Cancer Research Institute (NCRI) and the Independent Cancer Patients’ Voice (ICPV). EB was regularly consulted during the design of this pilot trial and on the acceptability of this research from a patient’s perspective. EB will continue to be a key partner throughout the implementation of this trial and the analysis of the findings.

This pilot trial will be conducted in three consecutive phases: preparatory phase, intervention delivery and data collection phase, and evaluation phase (Table 1).

**Table 1 Tab1:** Phases of the Mini-AFTERc pilot trial

Phase	Overview of procedures
Phase 1: Preparatory	• Development of SBCN intervention training programme • Delivery of training programme via a workshop for consenting SBCN in intervention centres • Development and testing of Mini-AFTERc smartphone application
Phase 2: Intervention delivery and data collection	• Screening and recruitment of patients at all centres • Intervention delivery at intervention centres • Collection of patient demographic and outcome data via smartphone app at baseline and 3 follow-up time points • Semi-structured interviews with SBCNs and sample of patient participants
Phase 3: Evaluation	• Statistical analysis of outcome data • Fidelity analysis of SBCNs adherence to intervention • Use of NPT in analysis of patient and nurse semi-structured interviews • Trial evaluation following the ADePT process

### Phase 1: Preparatory

The purpose of phase 1 is to develop the Mini-AFTERc intervention training programme for SBCN and to deliver the training at cancer centres that will be delivering the intervention. Additionally, a bespoke Mini-AFTERc smartphone application for the collection of research data will be developed and piloted during phase 1.

#### Mini-AFTERc intervention training

A detailed Mini-AFTERc training manual was developed for the previous Mini-AFTERc feasibility study [17]. This manual provides SBCNs with a detailed overview of the theory and structure of the Mini-AFTERc intervention, as well as providing examples of questions and prompts to aid SBCNs to facilitate intervention discussions with patients. The planned structure of the training sessions is as follows:

*Session 1*. Present an overview of the Mini-AFTERc intervention, fear of cancer recurrence and the purpose of the phone call. Trainees will be provided with a detailed explanation of the training manual, including the structure of Mini-AFTERc intervention and transcript examples of how to deliver the different stages of the intervention from previously recorded Mini-AFTERc telephone discussions (from the previous feasibility study [17]).

*Session 2*. An interactive workshop using roleplay scenarios representing each section of the Mini-AFTERc intervention. For each scenario, the initial stage is scripted and then SBCNs continue the conversation unscripted according to the Mini-AFTERc principles. SBCNs can “pause” and “restart” the discussion at any point to confer, clarify or reflect on their conversations and gain support and guidance from the trainers. This session also provides SBCNs with training in the use of the recording equipment and data collection requirements prior to beginning a Mini-AFTERc discussion.

*Session 3*. This session aims to simulate the Mini-AFTERc telephone discussion by using a patient expert and use of the recording equipment. Case studies have been written for the simulated patient. These scenarios were based on the clinical experience of GH. SBCNs deliver the Mini-AFTERc intervention as they would in their clinical practice setting; in a private room, over the telephone and using the audio recording devices. The SBCNs will receive a debrief from the lead researcher. Following a review of these recordings, a future meeting will be organised with each nurse participant to provide feedback.

All training sessions will be delivered by the research team based in Scotland. Following the formal training sessions, SBCNs will be offered continued support via email and telephone from the research team for the duration of the trial. Nurses will have frequent interaction with the research team during the trial and will be encouraged to feedback any challenges or difficulties they encounter during the trial. The research team will work with the nurses to find a suitable solution.

#### Smartphone application development

A bespoke smartphone application (app) will be designed to support data collection during this pilot trial. The app will be collaboratively developed by research team members in the Schools of Medicine and Computer Science at the University of St Andrews. The app provides a secure site for participants to electronically submit questionnaire responses throughout the trial. The app will send notifications to participants to prompt them to complete questionnaires at the pre-defined time points. A prototype of the app has been developed (Fig. 3). Early prototypes have been reviewed by the patient expert on the research team (EB) and informed its development. Throughout phase 1, the design and functionality will be continuously reviewed by all members of the research team.

**Fig. 3 Fig3:**
[figure not shown]
Screen captures of prototype Mini-AFTERc smartphone application

### Phase 2: Intervention delivery and data collection

#### Eligibility and recruitment

Mini-AFTERc is designed for patients with *moderate* FCR, therefore consented patients will complete the fear of cancer recurrence 4-item (FCR4) measure [27] to determine their eligibility (score range: 10‑14). The FCR4 has been previously shown to be reliable (*α* 0.93, 95% CI 0.91‑0.94) [27]. Any patient who score > 14 (i.e. high) on the FCR4 will be offered a referral onto psychological support services, in line with standard practice at each cancer centre. Additional patient eligibility criteria for screening are broad to ensure external validity of the sample. Patients will be eligible for screening if (1) they have completed their primary cancer treatment for breast cancer, (2) are cancer-free, (3) are female, (4) are aged 18 or over and (5) their responsible clinician agrees to their participation. Patients will be ineligible for screening if they have not completed their cancer treatment, are not cancer-free, are male and/or are receiving treatment for a diagnosed psychotic disorder that is known to the cancer service.

Potential participants will be identified in the cancer centres via patient appointment systems. A one-page study information letter will be sent to potential participants prior to their follow-up appointment or end of treatment review. There are two potential recruitment and consent processes:

*Process 1*. Participants attending in person will be invited to speak directly with a researcher about the study in the clinic. This meeting will provide study information and consent will be taken to participate in the trial.

*Process 2*. Participants not attending in person will have the study introduced by their cancer care team and be asked to consent to their contact details being shared with the research team. The researchers will contact potential participants to discuss the trial, provide additional information and consent. All study information and consent forms will be mailed. Consent forms will be required to be returned before participants can continue in the study.

#### Sample size

The trial aims to recruit 130 breast cancer patients, approximately 33 patients at each breast cancer centre. Researchers will screen patients until 65 patients have been recruited to the intervention group and 65 patients to the control group. Screening will continue until the target sample size has been reached. The anticipated recruitment period will take place over 12 months. An effect size of 0.5 at 0.85 power would require a sample of 130 patients to robustly demonstrate any effect of the intervention on patients’ fear of cancer recurrence, assuming a standard deviation of 7 between pre and post FCR measures, derived from a previous feasibility study [17], and an attrition rate of 30%.

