#### Screening and baseline assessment

Screening will be conducted with the fear of cancer recurrence 4-item (FCR4) measure [27]. Participant demographical information, including age (in years), cancer treatments received, education, employment and living situation, will also be collected during screening but eligibility will not depend on this information. A score of ≥ 10 and < 15 in the FCR4 is defined as ‘moderate’ FCR. Patients will be excluded from the trial if they score ‘low’ (< 10) or ‘high’ (≥ 15) on the FCR4. It is anticipated that 3 in 10 patients will obtain an FCR4 scoring in the moderate range (60th percentile) therefore approximately 440 participants will be required to be screened to obtain the required sample of 130. If eligible after screening, participants will be asked to complete the Hospital Anxiety and Depression Scale (HADS) [28] and the Euro-Qol 5-dimension health-related quality of life measure (EQ-5D-5 L) [29] at baseline. All initial screening and baseline data collection will be completed by the researcher and the participant either face to face or over the telephone.

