### Phase 3: Evaluation

#### Quantitative analysis

Data collected from self-report questionnaires will be quantitatively analysed using the STATA software [32]. A detailed CONSORT diagram will be completed with fully annotated reasons for withdrawal from the study and follow-up rates where possible. This will also include numbers referred onto further specialist services during the study. Descriptive statistics of questionnaire data will be reported and inferential statistics, including mixed regression modelling, will investigate outcome variable associations. Growth curve analysis (linear and polynomial parameters), will be performed using MPlus [33] to calculate the fear of cancer recurrence trajectory and intercept link intervention and control groups. Interclass correlation coefficient (ICC) will also be determined to estimate the potential power required for future trials, based on the number of clusters and sample size per cluster. The Monte Carlo modelling approach within MPlus, advanced by Bolger and Laurenceau [34], will be utilised to determine the sample size required to estimate for a moderate effect of the difference in trajectory (i.e. slope coefficient) between intervention and control groups with covariates (age, treatment experience, disease severity). Alpha set to 0.05 (2-sided). Analysis will not be blinded and will be conducted by the local research teams (St Andrews and Stirling Universities) who will seek advice from a divisional statistician (St Andrews).

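### The sample size of 130 does not follow from its stated inputs: with 30% attrition, an unadjusted two-group comparison has about 65% power for an effect size of 0.5, not 85%

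*Protocol article*

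**What the plan says.** All in the protocol article:

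- **Sample size.** "The trial aims to recruit 130 breast cancer patients". On the split: "Researchers will screen patients until 65 patients have been recruited to the intervention group and 65 patients to the control group". The justification is "An effect size of 0.5 at 0.85 power would require a sample of 130 patients to robustly demonstrate any effect" of the intervention on fear of cancer recurrence (FCR), "assuming a standard deviation of 7 between pre and post FCR measures", taken from the earlier feasibility study, "and an attrition rate of 30"%.
- **Quantitative analysis.** "Alpha set to 0.05 (2-sided"). This section plans mixed regression and growth-curve models, and the estimation of an intraclass correlation (ICC) to help plan future trials.
- **Trial design.** Two intervention centres are compared with two control centres, without randomisation.
- **Screening and baseline assessment.** "Patients will be excluded from the trial if they score" below 10 or at 15 and above on the FCR4, so every enrolled patient has a baseline FCR4 of 10 to 14.
- **Background.** The feasibility study had 16 patients.

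The sample-size paragraph names no test, no pre-post correlation and no allowance for centre.

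**The concern.** For a standardised effect of 0.5 at two-sided 0.05, about 64 per group is the familiar requirement for 80% power with nobody lost. A total of 130 is therefore close to the 80% figure before attrition, yet the paragraph presents it as the 85% figure after 30% attrition.

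A pilot need not be powered for effectiveness, but this one says that it is. A reader told 85% would take a null FCR result as fairly strong evidence against an effect of 0.5. At about 65% power, a true effect of that size is missed about one time in three (1 − 0.655 = 0.345).

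A smaller question concerns the standard deviation of 7. The paragraph does not say which FCR instrument it was measured on, or whether it suits patients selected within a narrow FCR4 band.

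**Working it through.** **Inputs.** Effect size d = 0.5, read as standardised; power 0.85; 130 recruited, 65 per group; attrition 30% (all from Sample size). Alpha 0.05 two-sided (Quantitative analysis). Two independent groups (Trial design).

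**1. Attempt to reproduce 130.** The normal approximation is n per group = 2 × [(z₀.₉₇₅ + z₀.₈₅) / d]².

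- 2 × [(1.960 + 1.036) / 0.5]² = 71.8, so 72 per group. The t-test gives 72.8, so 73 per group and 146 in total.
- Allowing for attrition: 146 / 0.7 = 208.6, so about 209 recruited (144 / 0.7 = 206 by the normal approximation).

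The figure of 130 is not reproduced. Other routes:

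| Route | Total recruited |
|---|---|
| Two-sided, 85%, inflated by × 1.3 instead of / 0.7 | 188 |
| One-sided 0.05, 85%, / 0.7 | 166 |
| One-sided 0.05, 85%, × 1.3 | 151 |
| Within-group paired test, 36 per group, / 0.7 | 104 |
| One-sided 0.05, **80%**, × 1.3 | 130 |
| Baseline-adjusted, correlation 0.6, 46 per group, / 0.7 | 132 |

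Only the last two come close. The first of them contradicts both the stated power and the two-sided alpha. The second needs a correlation that the document does not give.

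**2. Power that 130 delivers.** Analysed: 130 × 0.7 = 91, or 45.5 per group. Power ≈ Φ(d × √(n/2) − 1.96).

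- With attrition: Φ(0.5 × √22.75 − 1.96) = 66.4%; t-test 65.5%.
- With no attrition, 65 per group: 81.3%; t-test 80.8%.
- Effect detectable with 85% power at 45.5 per group: 0.635, or about 0.64.

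The 85% is missed even before the plan's own attrition is applied.

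**3. What could move the figure** (45.5 per group, t-test; every correlation and ICC here is an assumption).

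| Assumed correlation | Baseline-adjusted | Mean of three follow-ups, no baseline adjustment |
|---|---|---|
| 0.3 | 70% | 90% |
| 0.5 | 78% | 82% |
| 0.6 | 84% | 79% |

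The correlation is pre-post in the second column and between follow-ups in the third.

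Clustering works the other way. With 91 / 4 = 22.75 analysed per centre, the design effect is 1 + 21.75 × ICC. At ICC 0.01 it is 1.22 and unadjusted power is about 57%; at ICC 0.05 it is 2.09 and power is about 36%.

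**4. The standard deviation of 7.**

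- If 0.5 is standardised, the SD does not enter the power. It only implies a difference of 0.5 × 7 = 3.5 points.
- If 0.5 meant raw points, 2 × [7 × (1.960 + 1.036) / 0.5]² gives about 3,520 per group, so that reading does not yield 130 either.
- Scores confined to 10–14 have an SD of at most (14 − 10) / 2 = 2. Since SD(change) ≤ SD(pre) + SD(post), a change SD of 7 on the FCR4 needs a follow-up SD of at least 7 − 2 = 5.
- The document gives no FCR4 range. If the scale spans 16 points (assumption), the largest possible SD of change from a fixed baseline is 8, and a uniform spread gives 16 / √12 = 4.6.

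**The case against.** **The planned analysis is not a t-test.** Mixed models and growth curves over baseline and three follow-ups can be more efficient, so 65% is the power of one simple comparison and not of the trial's own model. This stands, and the corrected text must name the test. It does not rescue the paragraph, which states neither that model nor any correlation. The same planned analysis also recognises centre as a cluster, which lowers power.

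**The aims are feasibility and acceptability.** None of the three objectives tests effectiveness. This is true and limits the consequence, but the paragraph still makes an explicit power claim that its inputs do not support.

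**Two stronger readings are tempting.** A reader might infer that an SD of 7 cannot describe FCR4 change in patients selected at 10–14, and should be struck out. The documents do not support that. The paragraph speaks only of FCR measures without naming the FCR4, gives no scale range, and the bound requires only a follow-up SD of at least 5. That looks large but is not impossible. A reader might also infer that a 3.5-point target would carry over into the sizing of the full trial. The plan states no such target, and Quantitative analysis bases the future sample size on Monte Carlo modelling of a slope difference.

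**Conclusion.** The power statement is wrong as written. For a standardised effect of 0.5 at two-sided 0.05 with 30% attrition, 130 recruited gives about 65% power in an unadjusted comparison of two independent groups; 85% would need about 209. No variant that uses all the stated inputs gives 130.

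The 65% assumes equal groups, independent patients and no baseline or repeated-measures adjustment. The power of the planned model could be higher or lower and cannot be fixed from the document, because the correlation and ICC are not stated.

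The SD of 7 is a query about source and relevance. It is not a demonstrated error, and it does not affect the power result.

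**What to change.** Keep 130 and restate the sample-size paragraph along these lines: *130 recruited, about 91 analysed; about 65% power for a standardised effect of 0.5 (85% for 0.64) in an unadjusted two-group comparison at two-sided 0.05, before any gain from baseline or repeated-measures adjustment and before allowing for centre clustering.* Delete the claim that this size would robustly demonstrate an effect.

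If a higher power is to be claimed, name the model and give the correlation and ICC that it assumes.

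State which instrument and population the SD of 7 comes from, note that the source had 16 patients, and say whether it is thought to apply to patients selected at FCR4 10–14.

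The cost is one rewritten paragraph and a less favourable stated power. Recruitment, procedures and analyses are unchanged.

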#### Screening and baseline assessment

Screening will be conducted with the fear of cancer recurrence 4-item (FCR4) measure [27]. Participant demographical information, including age (in years), cancer treatments received, education, employment and living situation, will also be collected during screening but eligibility will not depend on this information. A score of ≥ 10 and < 15 in the FCR4 is defined as ‘moderate’ FCR. Patients will be excluded from the trial if they score ‘low’ (< 10) or ‘high’ (≥ 15) on the FCR4. It is anticipated that 3 in 10 patients will obtain an FCR4 scoring in the moderate range (60th percentile) therefore approximately 440 participants will be required to be screened to obtain the required sample of 130. If eligible after screening, participants will be asked to complete the Hospital Anxiety and Depression Scale (HADS) [28] and the Euro-Qol 5-dimension health-related quality of life measure (EQ-5D-5 L) [29] at baseline. All initial screening and baseline data collection will be completed by the researcher and the participant either face to face or over the telephone.

#### Intervention delivery

Patients will receive the Mini-AFTERc intervention telephone call from one of the trained breast care nurses within 2 weeks of screening. Patients will be given a date and time for the telephone call from the researcher on the day of screening. Telephone calls will last approximately 30 min and will be audio recorded by the nurse. Nurses may have consulted patients during their treatment and have access to their records during the intervention discussion.

#### Follow-up assessment

Participants in the intervention group will complete the consultation and relational empathy (CARE) [30] and the medical interview satisfaction scale (MISS) [31] within 1 or 2 weeks following their telephone discussion to measure acceptability. Additionally, the intervention group will complete the HADS and EQ-5D measures at 2 weeks, 1 month and 3 months following the intervention telephone discussion. Participants in the control group will complete the same measures at 3 weeks, 5 weeks and 13 weeks following baseline. The minor time point differences are to ensure data are collected at a similar time point in the study for intervention and control groups, allowing time for the intervention to be delivered. See supplementary file 1 for a comprehensive overview of all patient outcomes assessed in with research questionnaires.

All follow-up measures will be accessed by patients using the smartphone app. The app will be installed on the participants’ mobile phone after recruitment. To accommodate participants who cannot attend in person or do not have a compatible smartphone, a web browser version of the app has been developed or paper versions of the questionnaires can be made available. Alternative arrangements have been put in place to distribute paper copies at the different time points, due to technical difficulties with the smartphone application or participant preference.

#### Semi-structured interviews

Interviews with patients will cover their experiences during the recruitment process and during data collection, including timing and methods of collection (mobile phone app or paper-based). Patients in the intervention group will be asked about the usefulness and impact of the Mini-AFTERc intervention, including the method of delivery (telephone call), and ways to improve the intervention. Interviews with SBCNs will explore their views on the usefulness and impact of the intervention and areas where more help was required.

A 20% sample of patients (approximately 26) will be interviewed. A sampling matrix (see supplementary file 2) will ensure a representative sample of patients is recruited based on age, research site, trial group (control/intervention), and retention post-screening (attended/ dropped-out). All breast cancer nurses who delivered the intervention will also be invited for an interview.

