**Methods:**

This study will run in four breast cancer centres in NHS Scotland, two intervention and two control centres. SBCNs at intervention centres will be trained to deliver the Mini-AFTERc intervention. Female patients who have completed primary breast cancer treatment in the previous 6 months will be screened for moderate FCR (FCR4 score: 10‑14). Participants at intervention centres will receive the Mini-AFTERc intervention within 2 weeks of recruitment. SBCNs will audio record the intervention telephone discussions with participants. Fidelity of intervention implementation will be assessed from audio recordings. All participants will complete three separate follow-up questionnaires assessing changes in FCR, anxiety, depression and quality of life over 3 months. Normalisation process theory (NPT) will form the framework for semi-structured interviews with 20% of patients and all SBCNs. Interviews will explore participants’ experience of the study, acceptability and usefulness of the intervention and factors influencing implementation within clinical practice. The ADePT process will be adopted to systematically problem solve and refine the trial design.

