## Methods

### Aim and objectives

The aim of this pilot trial is to investigate the acceptability and feasibility of delivering the Mini-AFTERc intervention in every day clinical practice. The objectives are as follows:
To develop a procedure for training SBCNs in the delivery of the Mini-AFTERc intervention.To assess the acceptability of the Mini-AFTERc intervention for SBCNs and patients and the feasibility of introducing the intervention into current NHS service provision.To apply a formal decision-making framework to identify potential difficulties in the implementation of the pilot trial and appraise solutions prior to the development of a full-randomised control trial.

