#### Qualitative analysis of interviews

The primary aim of the interviews is to assess the acceptability of the intervention to participants and the feasibility of incorporating the intervention into current NHS service provision. All interviews will be recorded on digital recorders and transcribed verbatim.

The interview schedule and analysis will be informed by normalisation process theory and its four main tenets: coherence, cognitive participation, collective action and reflexive monitoring [37]. It provides a constructive approach to explain and evaluate the underlying mechanisms of the implementation process and the components used to provide information for the optimisation of trial parameters [37]. The research team has experience of using NPT in the area of FCR among nurses [18]. However, further adaptation will be undertaken to align the component parts for the participant interviews.

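### The Methods invite for interview only nurses who delivered the intervention, while the abstract promises all SBCNs; a trained nurse who made no calls would be missed, so the nurse evidence risks being selective

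*Protocol article*

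**What the plan says.** The article describes the nurse interview population in three places.

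- Semi-structured interviews (Methods, Phase 2): "All breast cancer nurses who delivered the intervention will also be invited for an interview".
- Abstract, Methods: "semi-structured interviews with 20% of patients and all SBCNs", with no condition on delivery.
- Table 1, Phase 2 row: "Semi-structured interviews with SBCNs and sample of patient participants", with no further definition.

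Two other statements show who could fall between these descriptions. Table 1 lists under Phase 1 "Delivery of training programme via a workshop for consenting SBCN in intervention centres". The section on intervention delivery says "Patients will receive the Mini-AFTERc intervention telephone call from one of the trained breast care nurses within 2 weeks of screening".

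The purpose of the interviews is also stated. The second objective is "To assess the acceptability of the Mini-AFTERc intervention for SBCNs and patients and the feasibility of introducing the intervention into current NHS service provision", and the section on qualitative analysis says "The primary aim of the interviews is to assess the acceptability of the intervention to participants and the feasibility" of bringing it into NHS services. The third objective is to find implementation difficulties before a full trial. Under the pilot trial evaluation, the interviews with patients and nurses feed the ADePT decision process.

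**The concern.** Whether a trained nurse goes on to make calls is itself a feasibility outcome. A rule that selects interviewees on that outcome leaves out the nurses who could say why delivery did not happen, and their account bears directly on the second and third objectives.

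The article takes more care with patients. In the paragraph that sets the nurse rule, the patient sampling matrix covers people who dropped out as well as those who stayed. Nurses have no equivalent.

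At stake is the pilot's conclusion about fit with routine practice. If some trained nurses never deliver and are not interviewed, the ADePT appraisal may miss barriers that the later randomised trial would then meet. Analysis cannot repair this, because the interviews would not exist.

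**Working it through.** The article states no figure for nurses, so there is none to reproduce. The only number near the rule is the patient interview target, and it is consistent: 0.20 × 130 = 26. The check is therefore mainly a comparison of texts.

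**Step 1. Do the statements agree?** The abstract sets no delivery condition, Table 1 is silent, and the Methods require delivery. They do not agree.

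**Step 2. Can the populations differ in practice?** Training goes to consenting nurses at the two intervention centres. Each call is then made by one of those trained nurses. Nothing requires every trained nurse to make a call. A trained nurse with no calls is therefore possible, and the Methods rule would not invite that nurse.

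**Step 3. Does another planned source cover that nurse?**

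| Source in the article | Covers a trained nurse with no calls? |
|---|---|
| CARE and MISS questionnaires | No; completed by patients |
| Fidelity measure | No; applied to transcripts of recorded calls |
| Debrief and feedback meeting after simulated delivery | Yes, but part of training; no analysis described |
| Contact with the research team during the trial | Yes, but informal problem-solving; no analysis described |
| Nurse interviews | Not under the Methods rule |

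The interviews are thus the only formally analysed source of nurses' own views that the article describes.

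**Step 4. Direction and size, under assumptions.** Let q be the share of trained nurses who never deliver, and let pD and pN be the shares favourable among deliverers and non-deliverers. The documents give none of the three.

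- Favourable share among all trained nurses: (1 − q) × pD + q × pN
- Favourable share among those invited under the Methods rule: pD
- Difference: pD − [(1 − q) × pD + q × pN] = q × (pD − pN)

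| q (assumed) | pD − pN (assumed) | Overstatement |
|---|---|---|
| 0 | any | 0 |
| any | 0 | 0 |
| 0.10 | 0.20 | 0.10 × 0.20 = 0.02 |
| 0.25 | 0.20 | 0.25 × 0.20 = 0.05 |
| 0.50 | 0.50 | 0.50 × 0.50 = 0.25 |
| 0.25 | −0.20 | 0.25 × (−0.20) = −0.05 |

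The last row shows that the sign reverses if non-deliverers are the more favourable group. The table only shows how the effect depends on q and on the difference in views. The interviews are theory-led and qualitative, and the article plans no such proportion.

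**The case against.** The case against has several parts.

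- **The excluded group may be empty.** Nurses are recruited and trained in order to deliver, and the two intervention centres share 65 patients. If each trained nurse makes at least one call, nobody is missed. This stands, and it makes the concern conditional.
- **Delivering is not the same as succeeding.** A nurse who made one call, struggled and stopped is still invited, and the interviews ask nurses where they needed more help. Barriers are therefore within scope. This stands against any claim that only nurses for whom delivery worked are heard. It does not bring in nurses with no calls.
- **Nurses have other routes to be heard.** There is training feedback and contact with the team during the trial, and the background cites a survey and interview study of 90 UK nurses. The first two have no described analysis. The third was completed before this pilot and cannot show why a nurse trained in it made no calls.
- **The abstract is condensed.** Read literally, all SBCNs would include control-centre nurses, who are not trained, so the Methods may simply be specifying which nurses are meant. That is plausible, but the specification chosen depends on delivery rather than training. The rule is stated explicitly, so it is not a detail left to a fuller document.

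A reader might infer that the nurse evidence is biased upward as a matter of fact. The documents do not support that: they do not say that any trained nurse will fail to deliver, or that such a nurse would think differently. A reader might also infer that nurses who declined training must be interviewed. They are outside the consenting group, and reaching them would mean recruiting and consenting a new one.

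**Conclusion.** The point holds as a conditional one. The abstract and the Methods state different nurse interview populations. The Methods version leaves out any intervention-centre nurse who was trained but made no calls, or withdrew before the first. The interview evidence on nurse acceptability and NHS feasibility therefore risks being selective. The favourable direction is the more likely one if reluctance or difficulty is among the reasons for not delivering, which is an assumption.

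The size is unknown. It is zero if all trained nurses deliver or if the two groups hold the same views, and it can reverse. Under the assumed ranges of 10% to 50% non-delivery and a 20 to 50 point difference, it is 2 to 25 points. The change is worth making because it is cheap and the lost evidence could not be recovered later.

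**What to change.** Make the abstract, Table 1 and the section on semi-structured interviews state one population: every SBCN trained in Mini-AFTERc at the intervention centres, whether or not that nurse delivered a call. Add reasons for non-delivery as a topic in the nurse interview schedule. Report the numbers trained, delivering and interviewed by centre beside the interview findings, so that a reader can see how much selection remains.

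The cost is a change of wording and at most a few extra interviews by the same team; if every trained nurse delivers, there are none. Some non-deliverers may decline, which the reported numbers would show. Interviewing nurses who declined training is not required.
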